### 2.6 Statistical analysis

#### 2.6.1 Estimation of circadian period.

We will use a symmetric sinusoidal regression model to estimate the fundamental period τ of the circadian pacemaker. The model will be fitted to salivary melatonin data, which serves as a proxy for the centrally governed circadian rhythm. The formulation of the regression model is as follows:

$$s_{\tau_{j}}(t)=m_{0}+a\cdot \sin\left(\frac{2\pi t}{\tau_{j}}\right)+b\cdot \cos\left(\frac{2\pi t}{\tau_{j}}\right)+\varepsilon$$
(2)

where *t* is the time passed since beginning of the protocol, measured is the average CBT. The three parameters to be fitted for each individual participant are the intercept or MESOR (Midline Statistic Of Rhythm) *m*_0_, and *a* and *b* which are the weights for the sine and cosine component, respectively. We will estimate multiple models, iterating over values of τ∈[20;28], and we will select τ with the best fit statistics *AIC*. The point estimate of τ will be propagated into the confirmatory models testing for a circadian rhythm in visual functions.

#### 2.6.2 Confirmatory analysis.

For our confirmatory hypotheses, we will examine two types of models. One model will test confirmatory hypotheses H1a–H1d investigating circadian rhythms in the PLR, and one model will be used to test hypotheses H2a–H2c concerned with circadian rhythms in the psychophysical thresholds. To test our hypotheses, we will always compare a full model incorporating a data generating circadian process, against a null model assuming a constant level in the dependent variable.

To test our hypotheses about the PLR, we will examine the ratio *R* of response amplitudes as a function of a participant’s circadian rhythm by calculating the Bayes factor of the comparison between a full model and the null model. The circadian rhythm is modelled with a sine-cosine parameterisation using the point estimate τ from eq. (2). The null model without the circadian components is defined, as

$$R_{j}(t)=m_{0}+u_{0j}+\varepsilon$$
(3)

while the full model with the circadian components is defined as

$$R_{\tau_{j}}(t)=[m_{0}+u_{0j}]+[a+u_{aj}]\cdot \alpha_{\tau_{j}}(t)+[b+u_{bj}]\cdot \beta_{\tau_{j}}(t)+\varepsilon \;$$
(4)

where *m*_0_ is the overall intercept or MESOR (Midline Statistic Of Rhythm), *u*_0_ is the person-specific random intercept. The sine and cosine components α and β together represent amplitude and phase of the circadian rhythm of a person *j* with a person-specific period τ. They vary over time *t* with fixed effects *a* and *b* and random participant-specific effects *u*_*a*_ and *u*_*b*_, with $u_{a}∼𝒩(0,\sigma_{u_{a}}^{2})$, and $u_{b}∼𝒩(0,\sigma_{u_{b}}^{2})$. ε is the error term associated with the response of a person *j* at a specific time *t*.

Similarly, circadian modulation of psychophysical performance is assessed by testing for a circadian component in temporal contrast sensitivity *T*. The null model T(t) and the full model $T_{\tau_{j}}(t)$ are defined as in eqs (3) and (4) above. Model comparisons are conducted separately for low (2 Hz) and high (8 Hz) frequencies. While sensitivity differences between post-receptoral mechanisms are well-documented, there is currently no evidence to suggest frequency-dependent differences in circadian modulation. For the sake of parsimony, if results between low and high frequencies or across post-receptoral mechanisms differ, we will perform exploratory analyses. We will not enter sex, age, or demographic variables in our confirmatory analysis, as we do not see sufficient empirical evidence for confounding effects.

We will sample from the posterior distributions to obtain parameter estimates and derive amplitude (*A*) and phase angle (ϕ) of the proposed underlying circadian rhythm with

$$A=\sqrt{a^{2}+b^{2}}$$
(5)

and

$$\phi =\left\{ \begin{array}{cc} \arctan(\frac{-b}{a}), & a>0\\ \arctan(\frac{-b}{a})+\pi , & a<0\text{ and }b\geq 0\\ \arctan(\frac{-b}{a})-\pi , & a<0\text{ and }b<0\\ -\frac{\pi }{2}, & a=0\text{ and }b>0\;\\ +\frac{\pi }{2}, & a=0\text{ and }b<0\; \end{array}\right.$$
(6)

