#### 2.1.3 Sample size.

This study will follow a within-person design. Each participant provides eleven repeated measurements. We will determine evidence for our hypotheses using a sequential Bayesian sampling strategy, such that data collection will continue until evidence strength suffices, or until a maximum of twelve participants. This maximum sample size is set by resource limitations. For the sequential sampling strategy, we will use Sequential Bayes Factor (BF) of the statistical model testing circadian modulation of melanopsin-dependent pupil constriction. The stopping criterion is BF > 10 or BF < 1/10 to quantify evidence strength for or against a circadian effect.

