### 2.3 Study duration & timeline

Each person participating in the study will be enrolling for a total of three weeks, consisting of continuous field measurements and one in-laboratory screening and two separate visits for control and experimental sessions.

After getting in touch with the study team, participants will first complete an online screening via the online platform REDCap [28,29]. The data from the online questionnaires or experience sampling is submitted to a REDCap server that is set up and maintained by the Chronobiology & Health team at TUM. It is set up as a virtual machine hosted by the Leibniz-Rechenzentrum der Bayerischen Akademie der Wissenschaften. If their answers comply with the inclusion and exclusion criteria, they will be invited for an in-person screening and, upon inclusion in the study, for two in-laboratory visits to take part in experiments. For an overview of the study participation, see Fig 1.

The online screening will be complemented by an in-person screening by a psychologist to confirm eligibility for the study. Since the forced-desynchrony protocol places participants in an exceptional environment, our inclusion criteria, the screening process, and procedures to ensure continued welfare are guided by suggestions from literature [30,31].

Upon inclusion in the study, participants will start a two-week long circadian stabilisation period. They will be invited for a first evening experimental session, the light exposure session, one week into the circadian stabilisation and one week before the forced-desynchrony session. Visual tests will be administered throughout the evening that achieve an experimental light exposure similar to the tasks administered during a wake period of within the forced-desynchrony session. The light exposure session also provides opportunity for the participant to get accustomed to the measurement instruments and prevent novelty or perceptual learning during the main study. After the evening session, participants will stay in the lab for a full night of sleep as their first adaptation night. Circadian outcomes from this session, including dim-light melatonin onset (DLMO) and core body temperature (CBT), as well as vigilance tests will be compared to those of an evening session under dim-light conditions. The purpose of this comparison is to quantify the potency of the light exposure during the protocol to elicit a circadian phase shift (for more information, see Sect 2.4.2).

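### BF > 10 supports a rhythm in some or all participants, not necessarily the shared rhythm that A and phi describe; report the two component Bayes factors, and add a linear block term

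*Protocol article*

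**What the plan says.** Section 2.6.2 tests every confirmatory hypothesis by a Bayes factor for a full model "against a null model assuming a constant level in the dependent variable". Equation (3), introduced with "The null model without the circadian components is defined", has an overall intercept, a person-specific intercept and an error. Equation (4) adds the sine and cosine terms, each with a fixed effect (a, b) and a participant-specific random effect (u_a, u_b). For contrast sensitivity T, the null and full models "are defined as in eqs (3) and (4) above".

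Amplitude A and phase phi (equations 5-6) are written in a and b. Section 2.1.3 applies the same comparison to melanopsin-dependent pupil constriction: "The stopping criterion is BF > 10 or BF < 1/10 to quantify evidence strength for or against a circadian effect". The maximum is 12 participants, and "Each participant provides eleven repeated measurements".

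Neither equation has a block or time-on-protocol term. Practice and fatigue are handled by design: section 2.3 uses the light exposure session to "prevent novelty or perceptual learning during the main study", and section 1.3 relies on regular naps.

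**The concern.** The Bayes factor and the reported parameters answer different questions. The Bayes factor rises if participants share a rhythm, if they have individual rhythms with scattered phases, or both. A and phi, as written, describe only the shared part. The article does not say how to read a large Bayes factor beside an amplitude near zero and an ill-determined phase. Sampling could stop, and a circadian effect be reported, while the accompanying A and phi show no such effect.

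A second, smaller matter is drift. The session covers less than two circadian cycles, so a steady practice or fatigue trend is not orthogonal to the sine and cosine. Without a term of its own, part of it passes into A and the rest into the error.

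**Working it through.** **Design inputs.** Blocks start every 3.75 h over 40 h: (40 - 2.5)/3.75 + 1 = 11 blocks, as stated. The protocol covers 40/24 = 1.67 cycles; first to last block start is 37.5/24 = 1.56.

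**Assumed inputs.** The article gives no SDs or priors. Residual SD is set to 1. The priors for a and b are normal with SD 0.5 or 1, and the period is close to 24 h. There were 120 to 400 simulated trials per cell (Monte Carlo error up to about 5 points), each evaluated once at n = 12 without sequential looks. Ranges below span the prior and variance settings tried.

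**What the Bayes factor tests.** Let S be the slopes-only model m0 + u_0j + u_aj*alpha + u_bj*beta + error. Because a Bayes factor is a ratio of marginal likelihoods,

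BF(eq. 4 vs eq. 3) = BF(eq. 4 vs S) x BF(S vs eq. 3).

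The first factor concerns a and b, the second individual rhythms. The planned figure is their product and cannot show which one made it large.

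**Size with a = b = 0.** With independent normal slopes of SD s, individual amplitude averages s x sqrt(pi/2) = 1.253s.

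| Slope SD | Mean individual amplitude | P(BF > 10), planned | P(BF > 10), eq. 4 vs S |
|---|---|---|---|
| 0 | 0 | 0-2% | 0% |
| 0.3 | 0.38 | 7-11% | 0-2% |
| 0.5 | 0.63 | 36-58% | 0-3% |
| 0.7 | 0.88 | 86-91% | 0-2% |
| 0.75 | 0.94 | 84-95% | 1-7% |
| 1.0 | 1.25 | 99-100% | 0-2% |

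At slope SD 0.75, with prior SD 0.5 for a and b and a half-normal 0.5 prior on the slope SDs, the median planned BF was about 9,200 and the median BF for a and b was 0.36.

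**Trend.** Let D be the start-to-end change and regress D x (k - 5)/10, k = 0 to 10, on intercept, sine and cosine.
- At tau = 24 h the coefficients are -0.029D and -0.144D, so the spurious amplitude is sqrt(0.029^2 + 0.144^2) x D = 0.147D. A 2-SD trend gives 0.29 residual SD.
- The rhythm terms absorb 12% of the trend's variance. The trend's variance over blocks is 0.1D^2, so a 3-SD trend adds 0.88 x 0.9 = 0.79 to a residual variance of 1.
- With no rhythm and a linear trend, P(BF > 10) was 1-2% for D = 0.5 to 1.5 SD, 3-7% at 2 SD and 7-23% at 3 SD. For an exponential practice curve it was 2-17% at 2 SD and 19-48% at 3 SD. With a linear term in both models these fell to 0-2%.
- With a true amplitude of 0.3 SD and a 3-SD trend, the linear term raised P(BF > 10) from 11% to 27% (prior SD 0.5) or from 3% to 11% (prior SD 1).
- The term multiplies the variances of a and b by 1.004 and 1.129 at tau = 24 h; the larger ratio is 1.156 at tau = 20 h.

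**The case against.** A reader might infer that the table shows false positives and that equation (3) should be replaced by the slopes-only null. The documents do not support that. In every row with a non-zero slope SD each participant truly has a rhythm; only the phases are scattered. Section 1.4 hypothesises circadian effects, section 2.1.3 speaks of evidence for or against a circadian effect, and section 2.6.2 models the outcome as a function of the individual participant's rhythm. None requires a common phase. A constant level is the exact complement of that omnibus hypothesis, and with no rhythm in anyone the planned test reached BF > 10 in only 0-2% of trials.

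Replacing the null would also cost real detections. Time runs from protocol start and the equations show no alignment to melatonin onset, so phase differences fall into u_a and u_b. With an assumed between-person phase SD of 4 h, switching the null cut P(BF > 10) from 87% to 24%, from 70% to 20% and from 64% to 26% in three settings. At slope SD 0.7 and prior SD 1, the slopes-only null gave BF < 1/10 in 50% of trials, against 2% as planned. Even a consistent rhythm of 0.5 SD lost power (68% to 57%, or 59% to 46%). This part of the objection stands in full.

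It is also fair that the article does not rule out reporting individual rhythms, since the posterior under equation (4) includes u_a and u_b. What remains is that A and phi are written in the fixed-effect symbols, with no rule linking them to what the Bayes factor supports.

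On the trend, a reader might infer that drift invalidates the rhythm test. It does not. Familiarisation and naps reduce drift, the stopping outcome is a reflex, and R is a ratio to light flux that may cancel shared drift. T has no such normalisation, so the point matters chiefly there.

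**Conclusion.** The point holds as one of interpretation. The planned Bayes factor jointly tests a, b and two slope variances, so BF > 10 alone does not license reading A and phi as a shared rhythm. How often the two would part company depends on the between-person slope SD, which the article does not give: rarely at 0.3 residual SD, in about a third to over half of trials at 0.5, and in most at 0.7. These rates rest on assumed SDs and priors and ignore sequential looks. The stopping rule may stay on the planned comparison.

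The missing block term is secondary. The leakage of 0.147 times the total change follows from the block schedule at tau = 24 h without any assumed SD. False BF > 10 becomes material only for trends of about 2-3 residual SD, a size for which the documents give no evidence; the likelier effect is lost sensitivity. Both changes are inexpensive improvements, not corrections of an error.

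**What to change.** 1. Keep equation (3) versus equation (4) as the omnibus test and for stopping, and state that it tests for a rhythm in some or all participants.
2. For each hypothesis report two further Bayes factors: equation (4) versus m0 + u_0j + u_aj*alpha + u_bj*beta + error (common rhythm), and that slopes-only model versus equation (3) (individual rhythms).
3. Interpret A and phi as a shared rhythm only when the first added Bayes factor supports a and b.
4. Add centred block number as a linear fixed effect to all models compared, chiefly for T.

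Cost: one extra model per hypothesis, some wording, and up to about 13% more variance in a or b at tau = 24 h (about 16% at 20 h). Without a trend the loss was negligible: for a common rhythm of a = 0.5 with slope SD 0.2, P(BF > 10) for the planned comparison moved from 70% to 68%, within Monte Carlo error.

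### Eq. (6) swaps +π and −π for a < 0, so linear summaries of posterior phase draws fail when the posterior crosses a = 0 (minor)

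*Protocol article*

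**What the plan says.** Section 2.6.1 (eq. 2) introduces a and b, "which are the weights for the sine and cosine component, respectively". Section 2.6.2 keeps that order in eq. (4): "The sine and cosine components α and β together represent amplitude and phase of the circadian rhythm", with a and b as their fixed effects. So a goes with the sine and b with the cosine throughout.

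After the model comparison, section 2.6.2 turns to estimation: "We will sample from the posterior distributions to obtain parameter estimates and derive amplitude" and phase angle. Amplitude is eq. (5), the root of a² + b². Phase is eq. (6), which has five rows:

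- a > 0: arctan(−b/a)
- a < 0 and b ≥ 0: arctan(−b/a) + π, in the equation source "b}{a})+\pi , & a<0\text{ and }b\geq 0"
- a < 0 and b < 0: arctan(−b/a) − π, in the equation source "b}{a})-\pi , & a<0\text{ and }b<0"
- a = 0 and b > 0: −π/2
- a = 0 and b < 0: +π/2

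The article does not say which form of the rhythm φ belongs to, or how the posterior draws of φ will be summarised. The period is person-specific and searched over 20 to 28 h ("iterating over values of τ∈[20;28").

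**The concern.** A five-row arctangent is written out to give one value per angle, on one range, without needless jumps. Eq. (6) does not do this. Its first, fourth and fifth rows belong to atan2(−b, a), while the ±π conditions in its second and third rows are those of atan2(b, a).

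The formula is meant for posterior draws, so a jump in the wrong place matters. If some draws have a slightly above 0 and others slightly below, they describe almost the same rhythm but receive values of φ about 2π apart. A plain average then lies between the two groups, and a plain percentile interval spans both. At stake is the reported circadian phase of the pupil response and of contrast sensitivity, not the tests for a rhythm.

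**Working it through.** **Inputs.** From the article: a is the sine weight, b the cosine weight, φ as in eq. (6), τ from 20 to 28 h. Assumed: posterior SD of a and b equal to 0.3 of the amplitude, with 0.15 and 0.5 as a range, and τ = 24 h for conversion to hours. The documents give no posterior SD.

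**Step 1: what φ should be.** Put a = A·cos φ and b = −A·sin φ. Then a·sin(2πt/τ) + b·cos(2πt/τ) = A·sin(2πt/τ − φ), so φ = atan2(−b, a). This agrees with the a > 0 row and both a = 0 rows of eq. (6).

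**Step 2: the a < 0 rows.**

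- For a < 0 and b > 0, −b/a is positive and its arctan lies in (0, π/2). Adding π, as printed, gives (π, 3π/2). The value on (−π, π] needs −π.
- For a < 0 and b < 0, the arctan lies in (−π/2, 0). Subtracting π, as printed, gives (−3π/2, −π). The value on (−π, π] needs +π.
- For b = 0 the printed value, π, is right.

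| (a, b) | eq. (6) | atan2(−b, a) | difference |
|---|---|---|---|
| (1, 1) | −0.25π | −0.25π | 0 |
| (−1, 1) | 1.25π | −0.75π | 2π |
| (−1, −1) | −1.25π | 0.75π | −2π |
| (1, −1) | 0.25π | 0.25π | 0 |

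As a approaches 0 from below with b > 0, eq. (6) tends to +3π/2, while its own a = 0 row says −π/2. With b < 0 it tends to −3π/2 against +π/2.

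**Step 3: single draws.** Every discrepancy is exactly one full cycle. Over 200,000 random (a, b) pairs, about 50% of the printed values fell outside (−π, π], but the largest difference from atan2(−b, a) modulo 2π was 9e−16. The printed φ rebuilds the curve in every sign case.

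**Step 4: linear summaries.** While b stays positive, each draw with a < 0 is shifted by 2π, so the linear mean moves by τ × P(a < 0). With SD 0.3 and τ = 24 h:

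- Centre (0, 1): P(a < 0) = 0.5, shift 24 × 0.5 = 12 h.
- Centre (0.2, 1): P = Φ(−0.2/0.3) = 0.252, shift 24 × 0.252 = 6.1 h.
- Centre (0.5, 0.87): P = Φ(−0.5/0.3) = 0.048, shift 24 × 0.048 = 1.1 h.

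Simulated draws agree:

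| Centre (a, b) | Mean off, eq. (6) | 95% interval width, eq. (6) | 95% interval width, atan2(−b, a) |
|---|---|---|---|
| (0, 1) | 12.0 h | 23.9 h | 4.8 h |
| (0.2, 1) | 6.0 h | 23.8 h | 4.7 h |
| (0.5, 0.87) | 1.1 h | 23.3 h | 4.8 h |

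The mean from atan2(−b, a) is essentially unbiased in all three. The last row shows that a tail is enough: once more than 2.5% of draws have a < 0, the upper percentile falls in the shifted group.

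For posteriors centred on a = 0, across SDs of 0.15, 0.3 and 0.5, eq. (6) gives a mean 11.7 to 12.0 h off, a median about 2 to 6 h off and an interval of about 24 h. With atan2(−b, a) the mean is 0 to 0.3 h off and the interval 2.3 to 9.8 h.

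**Step 5: circular summaries.** The circular mean of the eq. (6) draws is correct for every direction tested (error at most 0.01 h). Near φ = ±π, by contrast, the linear mean is about 12 h off under both the printed and the corrected formula.

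**Step 6: what φ refers to.** A·sin(2πt/τ − φ) peaks at t = τ(φ + π/2)/(2π), which is τ/4 after the time that φ marks: 20/4 = 5 h, 24/4 = 6 h, 28/4 = 7 h.

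**The case against.** The best defence is that no phase from eq. (6) is wrong: it differs from the principal value by a whole cycle, and an angle plus 2π is the same angle. The 12 h error needs draws to be averaged linearly, which the article does not say, and how angular draws are summarised is a detail that an article may leave to an analysis plan or code. Any single-valued phase formula also has a jump somewhere, so linear averaging can fail under the corrected version too.

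Most of this stands. It limits the point to a conditional consequence, and the silence on circular summaries is not itself the error. It does not rescue the equation as printed, whose rows disagree about the range of φ and which has three jumps (at a = 0 for each sign of b, and at b = 0 for a < 0) where one would do.

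Two stronger readings are tempting. A reader might infer that eq. (6) returns phases half a cycle wrong. It does not: the half cycle arises only from a linear mean over draws on both sides of a jump. A reader might also take φ for the time of peak and call it 6 h wrong. The article calls φ a phase angle, never an acrophase or time of peak, and with a on the sine it is a valid phase. Stating the reference curve is a clarification, and the gap is 6 h only at τ = 24 h.

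**Conclusion.** Eq. (6) is wrong as printed: the ±π conditions for a < 0 are swapped relative to the angle that the rest of the equation defines. The consequence is limited to linear summaries of posterior phase when the posterior crosses a = 0. There, at τ = 24 h and an assumed SD of 0.3 of the amplitude, the mean can be about 12 h off and the 95% interval about 24 h wide instead of about 5 h. With circular summaries the error disappears.

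The tests of H1a–H1d and H2a–H2c compare full and null models, and the stopping rule in section 2.1.3 uses a Bayes factor. Neither uses φ, and eq. (5) is unaffected. Severity is minor.

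**What to change.** Replace eq. (6) by φ = atan2(−b, a). If the rows are kept, use +π for a < 0 and b ≤ 0, and −π for a < 0 and b > 0. Add that φ is the phase in A·sin(2πt/τ − φ), with the peak τ/4 later (5 to 7 h for τ from 20 to 28 h). State that posterior draws of φ are summarised by a circular mean and a circular interval; the sign correction alone leaves the jump at ±π.

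The cost is one equation and two sentences. Data collection, the models and the tests do not change.

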#### 2.6.3 Exploratory analysis.

Effects found in the previously mentioned models will be further explored in additional analyses. Building upon the results from hypotheses H1a–H1d and H2a–H2c, we may further explore circadian effects specific in temporal frequencies for specific post-receptoral mechanisms. Additionally, we may confirm circadian effects in ocular structures and physiological parameters. Trajectories of ocular structures or summary statistics of physiological parameters may be included in post-hoc analyses as confounding factors in the model described in eq. (4) for hypotheses H1a–H1d, and for hypotheses H2a–H2c.

### 2.7 Ethical approval

The protocol has been reviewed and approved by the Medical Ethics Committee of the Technical University of Munich (2023-369-S-SB). All research will be conducted in accordance with the Declaration of Helsinki.

## 3 Discussion

### 3.1 Strengths and weaknesses of the protocol

Our protocol is uniquely geared to measuring circadian variations of retinal mechanisms while minimizing homeostatic effects. In evaluating our protocol, we highlight several points.

*Selection of pupillary response metrics and stimulation.* There are various measures of pupil kinetics that vary in their contribution of different photoreceptor classes: commonly, one differentiates between metrics of the pupillary light response and the post-illumination pupil response (PIPR) [57]. The contribution of different photoreceptor classes to pupil dynamics varies temporally and depending on stimulus design. The PLR is more focused on the initial constriction, while the PIPR is focused on the time period after offset of a light stimulus, including the redilatation phase. The PIPR measures the response to monochromatic light stimuli to no or a dim background, and offers common metrics to investigate dynamics of melanopsin-mediated visual functions. PIPR outcomes do allow to contextualize results better in previous literature. However, we have chosen the PLR because the experimental design associated with PIPR outcomes includes periods of dark adaptation and relies on long trials, unspecific photoreceptor activation, and little to no background illumination. To conclude, it forgoes the advantages of silent substitution, such as efficiency and specificity, for less complexity in experimental design.

*Known limitations in silent substitution.* The silent-substitution stimuli we use are nominally designed to stimulate specific photoreceptor classes. The precise contrast seen by the photoreceptor classes in the actual stimulus conditions can vary due to individual differences, which is difficult to characterise for an individual. As a consequence, our stimuli may contain some small residual contrast on the unstimulated photoreceptor classes. This is a well-known problem [47] but does not challenge the validity of silent-substitution measurements at large contrasts.

*Artificial laboratory conditions.* Due to the controlled nature of the experiment, participants are placed in an artificial environment, unable to fully represent real-world conditions. In particular, the experimental light conditions may have an impact on psychological variables in such a way that behaviour diverges from behaviour in natural settings. This is a limitation of any laboratory study, but a precondition for experimentally manipulating the mechanisms under investigation.

*Sample considerations.* In our study, we aim to recruit a total of twelve participants. As our study follows a strong within-subjects design, we believe that this sample size is appropriate to capture within-participant circadian influences on the outcome measures. Importantly, unlike many chronobiological studies, the present study is unique in that it strives to have a representative sample regarding distribution of sex (50% female participants). Due to unknown variations introduced by hormonal fluctuations, data required for comparisons will be collected at similar stages in the menstrual cycle, specifically during the mid-follicular phase (see Sect 2.4.2).

